### Participants Receiving MI Training

In these pilot implementation projects, we are assessing the use of MI among clinician and staff participants who have been trained to deliver the lifestyle interventions to mental health clients. Practitioners recruited from community mental health settings across Maryland will implement the 3 projects. Only English-speaking adults (aged ≥18 years) who provide informed consent are enrolled. Additional inclusion criteria include willingness to provide baseline data, attend training, implement the study intervention, and participate in follow-up data collection. Exclusion criteria across the 3 projects are minimal and exclude any staff who express an intention to leave the facility before project completion. ACHIEVE-D enrolled interested residential staff and employees at the PRP program as coaches. IMPACT participants include community mental health clinic staff (eg, licensed counselors, psychologists, and social workers) and prescribers (eg, nurse practitioners and psychiatrists). RHYTHM participants include PRP staff and health home nurses who are currently employed at the study sites.

### Ethics Approval

Approval to conduct the studies and the associated MI trainings was granted by the Johns Hopkins Institutional Review Board (IRB) protocols. ACHIEVE-D study received IRB approval in March 2021 (IRB00247344). IMPACT study received IRB approval in January 2021 (IRB00231836), and RHYTHM study received IRB approval in December 2020 (IRB00269855).

### MI Training

MI Training for the ALACRITY Center studies consists of 2 distinct approaches: real-time brief workshop training over videoconferencing and asynchronous avatar training.

#### Real-time Brief Workshop Training

##### Overview

Traditional introductory MI training is typically in person and is 16 to 24 hours long. However, based on the preferences expressed by stakeholders at study sites before initiating the projects, we present brief, real-time, and standard introductions to MI over videoconferencing uniquely tailored for each project. The MI trainer ([name]) is an MI practitioner, is a member of the Motivational Interviewing Network of Trainers (MINT), and has extensive experience in training practitioners who treat patients with SMI in the context of health services research. Following the guidelines recommended by MINT members [37], each training session invites the learners to consider why MI is useful in conversations around health behavior change and includes a definition of the method; a discussion of the MI spirit (ie, the accepting, compassionate, collaborative, and empowering style used in MI); an introduction to patient language related to change (change talk and sustain talk); and a brief overview of the following core MI skills: open-ended questions, affirmations, reflections, summaries, and collaborative information exchange [7]. Table 1 presents the real-time training content.

The amount of time devoted to each topic and opportunities for interaction vary by study. To increase the feasibility and acceptability of the workshops, the length of training for each project was negotiated in advance with the site leadership. ACHIEVE-D weight loss coaches will receive 4 hours of MI training. Psychiatrists prescribing smoking cessation pharmacotherapy in IMPACT will receive 1 hour of MI training; mental health counselors who provide the smoking cessation counseling will receive 2 hours of MI training. RHYTHM health home staff who implement the CVD risk reduction program will receive 4 hours of MI training.

**Table 1 table1:** Real-time training content.

	Study and the behaviors targeted by participants			
	ACHIEVE-D—weight loss	IMPACT—smoking cessation		RHYTHM—CVD^a^ risk reduction
	PRP^b^ staff	Prescribers	Counselors and Nurses	Health home staff
Participants, n	21	35	51	20
Training length (hours)	4	1	2	4
Training agenda	Why use MI?^c,d^ What does not help?^d^ Righting reflex Ambivalence Language of changed What helps?^d^ MI spirit Good practice video: MI skills occur with spirit^d,e^ MI skills: OARS^d,e^ Reflections guide the conversationd Responding to discord Introduce collaborative information exchanged Providing feedback Using leaders guides MI is not like a recipe Learning MI Introduction to the avatar	Why use MI?^d^ Ambivalence and change talk^d^ What helps?^d^ How MI works: Good practice video^d^ Brief review of core MI skills Collaborative information exchanged What it takes to learn MI Introduction to the avatar	Why use MI?^d^ What does not help?^d^ Righting reflex Ambivalence Language of changed What helps?^d^ MI spirit Good practice video: MI skills occur with spirit^d^ MI skills: OARS^d^ Introduce collaborative information exchanged MI is not like a recipe Learning MI Introduction to the avatar	Why use MI?^d^ What does not help?^d^ Righting reflex Ambivalence Language of changed What helps?^d^ MI spirit Good practice video: MI skills occur with spirit^d^ MI skills: OARS^d^ Reflections guide the conversation^d^ Responding to discord Introduce collaborative information exchanged Providing feedback Using leaders guides MI is not like a recipe Learning MI Introduction to the avatar

^a^CVD: cardiovascular disease.

^b^PRP: psychiatric rehabilitation program.

^c^MI: motivational interviewing.

^d^Included an interactive component (eg, chat response, poll, brief discussion, and practice exercise).

^e^OARS: Open-ended questions, Affirmations, Reflections, Summaries

##### Development

Owing to the advent of the COVID-19 pandemic, all MI trainings were modified from an in-person format to delivery over videoconferencing. Although there is not much known about how best to adapt the content of in-person experiential training workshops for this purpose, MINT members communicated ideas for the transition on the e-forum of their listserve [38]. Additional ideas for modifying training activities were offered during workshops, and a monthly virtual trainers meeting for sharing activities, ideas, and successes is ongoing for any interested MINT member. As a result of participation in these various collaborative conversations, the first author ([name]) modified several training activities for the videoconferencing format. One key consideration was how best to engage participants and encourage them to try different components of the MI method while being observed by others on screen rather than in the privacy of small groups. The trainer incorporates multiple activities, alternating training techniques to keep learners interested, including the use of written transcripts with change talk and sustain talk indicated in different colored fonts and small breakout rooms for practice exercises [39,40]. Efforts are made to switch styles every 20 minutes to best engage learners. Anonymous polling provides low-stakes opportunities for learners to select the most MI-consistent practitioner strategy in response to a vignette (eg, choose an evocative question, select the reflective listening statement, or identify the best example of a collaborative information exchange); the chat function allows the trainees, who may be less comfortable or quick to respond, opportunities to pose questions or respond to trainer requests.

All synchronous, real-time trainings will be held over videoconference and scheduled at a time that accommodates most practitioners at each site. As it is challenging to synchronize participants from multiple sites where the research is being conducted, for anyone unable to attend the real-time meeting, recorded Zoom sessions (Zoom Video Communications) will be made available for viewing. The first author developed a tailored handout resource packet with specific examples of how to use MI when discussing each project’s target behavior change; this material will be provided to practitioners to further support their MI skill acquisition during and after training.

#### Asynchronous Avatar Training

##### Overview

The ALACRITY Center partnered with a web-based experiential learning company, Kognito [32], to develop the asynchronous avatar training. This development process with Kognito took approximately 14 months and resulted in the products described in the following sections. After the completion of their real-time MI training, the practitioners are given access to the web platform and are encouraged to register for an account that houses their study-specific avatar training and simulation. The first component is a 12-minute didactic module, “Motivational Interviewing Techniques*,”* which uses an avatar coach to provide an overview of the method. This module is identical for each of the 3 projects and must be completed before the learners move on to the second part of the training, the conversation simulation. The participants are asked to complete their first conversation simulation as soon as possible after the real-time MI training and are prompted to use the platform throughout the study period.

Each study has 1 distinct conversation simulation that addresses the project’s respective behavioral target. All conversation simulations involve 3 characters (Figure 1). The avatar practitioner character is played by the study MI learner and discusses weight loss (ACHIEVE-D), smoking cessation (IMPACT), or cholesterol reduction (RHYTHM) with an avatar patient. The avatar patient has speech that is coded to be generated automatically; when the character stops speaking, there are 3 to 4 choices presented to the learner representing options that are more or less effective when using the guiding style of MI. Table 2 shows the learner response choices for the avatar weight loss simulation.

The avatar patient, the character that is not playable or maneuverable by the practitioner, is modeled after an atypical patient with SMI in a community mental health setting. Depending on the study, the avatar patient is obese, smokes tobacco, or has high cholesterol. The avatar patient responds to the practitioner in the way a typical client might respond as the practitioner selects one of the previous MI-consistent or non-MI directive choices. The third avatar character functions as a virtual coach who both narrates the didactic module and, when a response choice is selected by the practitioner, provides on-screen text guidance that either affirms the learner’s use of MI or, as needed, provides corrective suggestions to the learner as they engage in the respective conversations about weight loss, smoking cessation, or cholesterol reduction. Learners have the opportunity to undo their selection and pick a different option to see how such a change impacts the conversation flow.

The avatar platform includes several feedback features to assist learners in improving their MI skills. An on-screen meter registers and reinforces practitioners’ ability to cultivate change talk, a core skill that is essential in an MI interaction [7]. For example, if the practitioner says, “You’re aware of the health effects of smoking and they worry you enough to consider quitting” and the client responds, “Yea, I think about it...I used to smoke right after a shower but now I try to go longer...,” then the meter would indicate movement toward cultivating change talk. The simulations also include occasional thought bubbles; that is, a text appears above the avatar patient’s head and allows the learners to read the patient’s unspoken thoughts from the most recent exchange. This feature is most useful when the patient responds with silence, one-word answers, or if they appear hesitant to voice confusion over what is being discussed. As the learners move through the simulation, the platform keeps a tally of each practitioner’s choice; after completing the full simulation, there is a performance dashboard available to the learner on their use of MI spirit and skills. Learners are able to see their scores on the relational components of the MI spirit (partnership and empathy); adherence to the technical aspects of the approach (cultivating change talk and softening sustain talk); and their use of specific core MI skills, questions, and reflections (Figure 2). The participants are encouraged to practice their MI skills with the avatar at least monthly throughout the study.

**Figure 1 figure1:**
[figure not shown]
The avatar characters. MI: motivational interviewing.

**Table 2 table2:** Avatar weight loss simulation learner response choices.

Client statement and practitioner choice options		Practitioner strategy	Effective use of MI^a^ approach?
* **...I’m trying (to lose weight) and nothing’s happening!** *			
	*Why do you think you can’t lose weight?*	Question—confrontational	No
	*You’re frustrated that this is so difficult.*	Simple reflection of sustain talk	Somewhat
	*You’re frustrated and want to do something that helps you lose weight.*	Complex reflection—shifting focus	Yes
* **I get so tired climbing up all those stairs, my knee flaring’ up the whole way, that I just kind of eat whatever I want once I’m up there.** *			
	*It sounds like taking those stairs would be a great way to lose weight.*	Persuading	No
	*So, all those stairs are difficult for you.*	Simple reflection of sustain talk	Somewhat
	*Even when you’re tired or frustrated, you’re still doing what needs to be done. And it makes you realize that you wish you’d eat healthier.*	Complex reflection	Yes

^a^MI: motivational interviewing.

**Figure 2 figure2:**
[figure not shown]
The performance dashboard.

##### Development: The Avatar Characters

Early in the development process, members of the ALACRITY team who were the most familiar with the community mental health program environment provided Kognito with pictures of the study sites and descriptions of practitioners and patients seen at the sites. After a few iterations (eg, adjusting characters’ skin tone, patient affect, and voice speed), the project’s 3 avatar characters were created. The virtual characters were brought to life with animation, lip-synced speech, and the use of facial and hand gestures to demonstrate their nonverbal emotional responses. The images of the players are the same for each of the studies. The topics of conversation and the names and mannerisms of the virtual patient characters vary by study behavioral focus. The patient avatars were modeled after clients with well-controlled depression (ACHIEVE-D), schizophrenia (smoking cessation), and bipolar disorder (CVD risk reduction) who were seen at the community mental health programs.

##### Development: The Didactic Module

Kognito’s existing MI Techniques module formed the foundation for the product’s final didactic training; the first author modified the content to reflect the most current constructs in MI [7]. Clinician and client language tailored to each study’s target behavior was incorporated so that the practitioners would find the learning module more relatable. For example, to indicate that the patient was referring to changing their smoking- or weight-related behaviors, we included examples of the patient’s change talk statements such as “I need to cut back” or “I’d like to be able to move around more easily.”

##### The Feedback Mechanisms: The Performance Dashboard

The performance dashboard was designed to help learners know how well they use MI in their simulations. Study MI experts worked with Kognito to modify their existing automated scoring system so that it was better aligned with up-to-date MI training and feedback guidance. This was a multistep and iterative process. First, a careful review of the conversation scripts allowed the study team and Kognito to identify learner pitfalls. A pitfall by definition is when a practitioner selects a conversation strategy that is not likely to be effective when guiding the patient toward the desired behavior change (eg, if a practitioner chooses to ask an information-gathering question when a better response would be to provide a reflection). MI-nonadherent behaviors, such as persuading a patient to take a medication or confronting their lack of willingness to make a change, as well as reflecting on patient sustain talk, missing an opportunity to reflect on change talk, or failing to empathize with the patient, are coded as pitfalls. The team also identified examples of conversation targets for the learner. The targets are defined as the practitioner’s conversation choices that are the most consistent with MI in guiding the patient avatar toward the desired behavior change (eg, asking evocative questions, affirming the patient’s effort, and seeking collaboration before offering advice).

The study team was interested in having the automated performance feedback align with what is measured by the Motivational Interviewing Treatment Integrity Tool (MITI; version 4.2.1) [42]. MITI is a validated coding system that is used to assess MI skills and provide feedback to learners and is widely accepted as a treatment integrity measure for clinical trials involving MI. The tool has the following 2 components: global scores and behavior counts. Global scores capture the rater’s global impression or “gestalt” of the entire interview on 5-point Likert scales for the following 4 dimensions: Cultivating Change Talk, Softening Sustain Talk, Partnership, and Empathy. Because Artificial Intelligence is unable to characterize the “gestalt of a conversation,” the study team worked with Kognito to create separate matrices to classify the scoring for each of the MITI global domains. On the basis of the number of targets and pitfalls possible in each conversation type, we determined what combination of pitfalls and targets would comprise the grading criteria for each of the Likert scale scores (1-5). We decided to weight equally hitting the target and avoiding a pitfall. For example, if the domain of Partnership had a total possibility of 4 targets and 5 pitfalls during the weight loss conversation simulation, a *1* on the Likert scale would be assigned if the practitioner missed all the targets and hit every pitfall. A *5* on the Likert scale would be assigned if the practitioner avoided all the pitfalls and hit every target. We used this same mapping process to identify Likert score categories for each global domain for all the 3 conversation types.

MITI behavior counts are tallied instances of 10 specific practitioner behaviors including those that are categorized as MI-adherent (eg, emphasize autonomy, seek collaboration, and affirm) and MI-nonadherent (eg, confront and persuade). The human coder’s task is to simply count each instance of the clinician’s behavior during the segment being reviewed. The final step in the development of the automated scoring system for this study was to label each practitioner’s conversation choice as one of the 5 learner behaviors measured (eg, question, reflection, affirm, persuade, and confront); the automated system as currently developed was not built to provide counts for the 5 additional behaviors measured by MITI (ie, providing complex reflections, persuading with permission, giving information, seeking collaboration, and emphasizing autonomy).

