#### Measures

We adapted the *Beliefs about Motivational Interviewing* questionnaire [43] to assess participants’ beliefs about MI. The original scale asks participants to react to 7 statements about MI on a 5-point Likert scale from “Strongly Disagree” to “Strongly Agree.” We included the following two statements in our modified version: (1) “There is strong empirical support for motivational interviewing” and (2) “I am effectively implementing motivational interviewing.”

We created a 12-item questionnaire, *Importance and Confidence to Use MI.* The participants are asked about their perspectives on the importance of, and their self-reported confidence to use, MI skills. Example questions include, “Please rate how important is it for you to use motivational interviewing” and “Please rate how confident you are in your ability to use motivational interviewing to elicit behavior change in your patient.” Responses are chosen on a 5-point Likert scale from “Not at all” to “Extremely.”

We will use the MITI tool to measure clinician fidelity to MI from audiotaped standardized patient (SP) interviews [44-46]. Correlations between practitioners’ adherence to MI with real patients and SPs are moderate to large on most indexes of performance [47]. Practitioners will conduct interviews with SP actors playing the role of patients with SMI. SP actors will talk as if they are interested in either weight loss, smoking cessation, or CVD management according to the pilot project their practitioner interviewer is implementing. MITI scores will be determined by blinded, independent coders who were trained by the tool’s creators.

A study staff member blinded to other survey measures will extract data on practitioners’ automated scores from the performance dashboard at each data collection time point as another measure of adherence to MI.

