#### Analytic Plan

We will examine changes in the MITI from baseline to each subsequent time point to assess the change in practitioners’ skills in implementing MI. All SP interviews will be coded. A difference of 1 on a 5-point scale between pre- and posttraining scores for MITI global scores will be considered a clinically significant change in MI skills proficiency and will be used for statistical testing as the relevant effect size [42].

We will use a random 20-minute segment from the audiotaped SP interviews for coding as recommended by the creators of the MITI tool [42]. We will use a random calculator to ensure that the sampling of interviews that are >20 minutes is truly random so that proper inferences about the use of MI can be drawn.

We will examine changes in practitioners’ automated scores from completed avatar simulations from baseline to each follow-up time point.

We will also compare the associations of the MITI scores from the SP interviews with the Kognito-automated performance feedback metrics from a conversation simulation completed during the same time as the data collection window.

We will examine changes in participants’ beliefs about and the importance of using MI and their confidence to use its components with their patients.

Qualitative data from interviews and focus groups will be audio recorded and transcribed. Using thematic analysis [50], 2 research team members will identify meaningful segments within the responses and assign codes. We will then group these codes into themes, which will be examined by the research team.

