### Limitations

One limitation of the study is that none of the training methods have a comparator condition. The pretest-posttest outcomes are used here to assess the acceptability, feasibility, and effectiveness of the 2 training methods for improving practitioners’ MI skills.

Avatar practice requires practitioners to set aside time during their busy workdays. The extra workload and responsibilities of staff during the COVID-19 pandemic may leave little time or motivation for avatar skills practice after their initial exposure to MI, thus potentially decreasing the impact of this component of the training.

Another limitation is that because of the nature of the avatar platform and how the 3 conversations simulations are built, there are limited choice options. Therefore, after a learner has used the platform a few times, they might find it redundant and be less willing to practice. The didactic module and the conversation simulations may be a great opportunity for novice learners to practice their skills; practitioners with more experience in patient-centered counseling may be less interested in using a platform that offers few multiple-choice conversation options.

To overcome the challenges of assessing MI skills in implementation settings, we are using multiple measures, namely, MITI and the automated feedback scores from the avatar simulations. The feedback feature of the avatar simulations was originally designed to assist learners in improving MI skills. The mapping approach we used to create the automated scoring system for each of the global scores may limit the precision of the measure to capture how well the clinician is using MI. In addition, because participants complete the same simulations for training and assessment purposes, scoring from the simulations may not be a valid outcome measure of their MI skills.

This study design was in the context of implementation research and does not allow us to examine the effect of the MI workshop training component alone. However, examining MI in real-world settings is an innovative aspect of the study. Although there are limitations to asking about experiences of the training over a 6- or 12-month period, our qualitative interviews at the end of the study will add detail to the quantitative results.

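### The avatar global scores are analysed as 1-5 grades cut from finer counts that the platform already tallies, so change is measured less precisely than it could be

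*Protocol article*

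**What the plan says.** The section on the performance dashboard explains how the automated scores for the four MITI global domains are built. Choices in the simulation are classed as targets or pitfalls, and "we determined what combination of pitfalls and targets would comprise the grading criteria for each of the Likert scale scores (1-5". On weighting, the authors write: "We decided to weight equally hitting the target and avoiding a pitfall". The illustration supposes "a total possibility of 4 targets and 5 pitfalls during the weight loss conversation simulation" for the Partnership domain. A grade of 1 goes with missing every target and hitting every pitfall, and a grade of 5 with a perfect run. The rules for grades 2, 3 and 4 are not given. The same process was used for every domain and all three simulations.

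Under Measures, a blinded staff member "will extract data on practitioners’ automated scores from the performance dashboard at each data collection time point". The Analytic Plan then states: "We will examine changes in practitioners’ automated scores from completed avatar simulations from baseline to each follow-up time point". It also plans to relate the automated metrics to MITI scores from the standardized-patient interviews.

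The Overview of the avatar training says that "the platform keeps a tally of each practitioner’s choice". Under Limitations the authors concede: "The mapping approach we used to create the automated scoring system for each of the global scores may limit the precision of the measure".

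**The concern.** With equal weights, each domain has a natural raw score: targets hit plus pitfalls avoided. Cutting that count into five grades discards information before the analysis starts. A practitioner can improve on one item, sometimes on two, and show no change in grade. The five-level form suits learner feedback and resembles the MITI scale, but neither a change-from-baseline analysis nor an association with MITI needs it.

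Two things are at stake: the precision of the change analysis, and the strength of the observed association with MITI. Precision matters most if results are analysed by project or training group, because Table 1 lists groups of 21, 35, 51 and 20. The choice is made at extraction, so tallies that are never exported cannot be recovered later by an analysis plan.

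**Working it through.** The article states no power, alpha, standard deviation or sample-size calculation for the avatar scores, so there is no figure of its own to reproduce. Table 1 gives 21 + 35 + 51 + 20 = 127 practitioners, which matches the enrolment under Results.

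**Step 1: arithmetic that does not depend on the unpublished cuts.**
- Items in the example: 4 targets + 5 pitfalls = 9, so the count runs from 0 to 9 (10 values).
- One-item gains: 0 to 1, 1 to 2, and so on up to 8 to 9, which makes 9.
- An ordered map onto five grades, all of them used, has 4 boundaries. Only the 4 one-item gains that cross a boundary change the grade, so 9 - 4 = 5 of 9 do not.

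**Step 2: arithmetic that depends on how the anchors are read.**
- If grade 1 means only a count of 0, and grade 5 only a count of 9, then counts 1 to 8 (8 of 10) share three grades. At least one grade then spans three or more counts, so some two-item gains are hidden: 2 of 8 in each strict split tried. A three-item gain is hidden in only one of those splits (1-2 / 3-6 / 7-8).
- If the ten counts are split evenly, two per grade, then 6 of 10 counts fall in grades 2 to 4 and no two-item gain is hidden.

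**Step 3: power, first simulation.** Assumptions: paired counts, Binomial(9, p); a shared practitioner effect on the logit scale (SD 0.5 or 1.0) and an occasion effect (SD 0.4); baseline p of 0.35, 0.5 or 0.65; n = 20, 35 or 51; paired t-test, two-sided 5%. The shift was set to give about 80% power on the count. Strict splits of counts 1 to 8 were 1-3/4-5/6-8, 1-2/3-6/7-8, 1-3/4-6/7-8 and 1-2/3-5/6-8.

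| Score analysed | Power | Loss (points) |
|---|---|---|
| Count 0-9 | 0.79-0.80 | none |
| Grade, even split | 0.74-0.77 | about 3-5 |
| Grade, strict anchors | 0.65-0.74 | about 6-14 |

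**Step 4: power, second simulation with different assumptions.** Practitioner effect SD 0.7, no occasion effect, no clustering or dropout, the first three strict splits above plus the even split, 3,000 runs per setting.

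| n | Item success | Count | Grade (all maps) |
|---|---|---|---|
| 20 | 0.50 to 0.60 | 0.40 | 0.27-0.35 |
| 51 | 0.50 to 0.60 | 0.81 | 0.63-0.76 |
| 86 (35 + 51, both IMPACT groups) | 0.50 to 0.60 | 0.96 | 0.86-0.94 |
| 127 | 0.50 to 0.60 | 0.996 | 0.956-0.993 |
| 127 | 0.50 to 0.55 | 0.61 | 0.44-0.56 |

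At n = 51 the count has power 0.81. The even split loses 5 points (0.811 - 0.761) and the strict splits lose 9 to 18 (0.811 - 0.722 to 0.811 - 0.634), somewhat more than in step 3. Over all settings, the relative efficiency of the grade is 0.85-0.91 for the even split and 0.65-0.83 for the strict ones. That is equivalent to losing about 9% to 35% of the sample (1 - 0.91 to 1 - 0.65). Among practitioners whose count rises, about 18% to 44% show no change in grade.

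**The case against.** The 1-5 form is deliberate: the dashboard section says the aim was to align automated feedback with the MITI, whose global scores are on 5-point scales. The Limitations section already discloses limited precision. It also says simulation scores may not be a valid outcome, because the same simulation serves for training and assessment. The MITI from standardized-patient interviews is the validated skill measure. These points stand, and they make this a matter of efficiency for a supporting measure. But the disclosure changes no analysis, and an association with MITI does not require matching units.

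Several stronger readings are tempting, and the article does not support them:
- A reader might infer that real change will go undetected. It will not be lost altogether: every map tried detects group change with reduced power.
- A reader might take it as fact that eight of the ten counts share three grades. The anchors say when a 1 or a 5 is given, not that no other count earns it, so the larger losses are conditional.
- The 9-item count is an example for one domain. Item numbers for the other domains and simulations are not published.
- The dashboard also reports use of questions and reflections, so the point applies to the four global domains and not to all avatar data.
- No passage says that the avatar analysis is split by project or training group. If all practitioners are pooled, the loss is small for a moderate change.

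Feasibility also carries weight. The article says that choices are tallied, not that target and pitfall data can be exported. Scripts branch and learners may undo a selection, so counting rules are needed.

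**Conclusion.** The point holds in limited form. For the four global domains, the plan extracts and analyses a grade that is coarser than the record the platform keeps. That 5 of 9 one-item gains are hidden in the article's example needs only equal weighting and an ordered five-grade map. The power loss rests on assumed cuts, baseline level, correlation and test. From about 80% on the count it is about 3-5 points with an even split and about 6-14 points if grades 1 and 5 apply only at the extremes; the second set of assumptions gives up to 18 points at n = 51.

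The consequence is reduced precision, with small gains possibly missed, mainly in analyses of groups of 20 to 51. At n = 127 a moderate change is still detected with power above 0.95, although a smaller change (item success 0.50 to 0.55) loses 5 to 17 points (0.608 to 0.559-0.438). The analysis should be changed because the remedy is cheap; the coarsening does not make the planned analysis invalid.

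**What to change.** - **Measures:** extract the target and pitfall tallies for each domain as well as the dashboard grade, if the vendor can supply them. State how undone selections and branching paths are counted.
- **Analytic Plan:** for each domain, use (targets hit + pitfalls avoided) / (targets + pitfalls possible in that project's simulation) for the change from baseline and for the association with MITI. The dashboard section indicates that the numbers possible were set for each conversation type, so the denominators should be available.
- **Reporting:** give the 1-5 grade beside the proportion, for learner feedback and for comparison on the MITI scale.

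The cost is a wording change and a fuller data export, with no new participants, visits or raters. The proportion is not in MITI units, which is why the grade should still be reported. The change does not remove the limitation that one simulation serves for both training and assessment.
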